## Abstract

Cardiometabolic diseases are one of the primary causes of mortality and morbidity worldwide and sedentary lifestyles are contributing factors to these pathologies. Physical exercise has been recognized as an important tool in the prevention and treatment of these diseases. However, there are still some doubts about the efficacy of certain type of physical exercise programs for older participants. The main goal of this study is to assess the impact of different aquatic-based physical exercise programs on risk markers of cardiometabolic diseases in older people. The study group will consist of non-institutionalized individuals, within the age group of 65 or older. The sample will be randomly divided into four groups, three experimental groups (EG) and one control group (CG). Participants from the EGs will be exposed to three physical aquatic-based exercise programs for a period of 28 weeks (continuous aerobic, interval aerobic and combined). The evaluated parameters include anthropometry, physical functions, mental health, cognitive function, carotid arteries intima-media thickness, heart rate variability and biochemical markers. The results will allow an interpretation of the impact of different aquatic-based physical exercise programs on cardiometabolic diseases markers and can also be used as a tool for professionals to prescribe adequate and more efficient physical exercise programs.

## 1. Introduction

Ageing is considered a progressive and inevitable phenomenon, where the reduction in various physical and metabolic functions occurs [1]. As they age, humans become increasingly sensitive to certain pathologies such as cardiometabolic diseases. These diseases are considered to be the main cause of mortality and morbidity worldwide and have attracted great interest in various fields of scientific investigation. The World Health Organization (WHO) reports that cardiometabolic diseases are responsible for 63% of 57 million annual deaths, with a significant correlation of 6 to 10% of these deaths due to physical inactivity [2].

Nowadays, more than 60% of the elderly population live a sedentary lifestyle [3]. This contributes to physical and mental frailty. Physical frailty is characterized by a reduction in physical activity levels, unintended weight loss, fatigue, reduction in handgrip strength, and a decrease in walking speed [4]. The same authors characterize cognitive frailty as the decline in all functional mental abilities that regulate the lifestyle of an individual. These mental activities range from simple to complex. Both types of frailty are associated to the process of physical and mental decline, with a deterioration in physical and mental capabilities that may lead to a serious decrease in health conditions, loss of autonomy, institutionalization and mortality [5]. To counteract sedentary lifestyles, WHO has developed strategies for a more active and healthy society. These strategies include the creation of guidelines that state the frequency, duration, intensity, type and amount of physical activity that are recommended for different age groups. Such guidelines target the prevention of non-transmissible chronic diseases [6]. Simultaneously, there has been an increase in research using a set of variables that are related to these types of pathologies, such as body composition [7], functional fitness [8], and variables related to the cardiovascular [9], cognitive [4] and immune systems [10].

Physical exercise is considered an effective tool during the process of ageing, as it helps to stabilize the loss of physical and metabolic capacities, mitigates the overall progress of ageing and enables more autonomy. Various studies indicate that regular physical exercise plays an important role in the prevention and treatment of cardiometabolic and cognitive diseases [10,11,12,13,14].

Different studies have been conducted recently to verify the efficacy of various physical exercise programs (aerobic, muscular strength and combined) on variables related to these pathologies. Such studies have analyzed the impact of exercise on cognition, cardiovascular, metabolic, immunological, functional and mental levels [15,16,17,18]. However, most of these studies have focused on land-based exercise and have not involved specific aquatic exercise programs, which are popular and successful among older participants.

The present investigation and its specific experimental design using different types of aquatic-based exercise programs aims to assess the impact of different aquatic-based physical exercise programs on risk markers of cardiometabolic diseases in older people.

## 2. Materials and Methods

### 2.1. Design

This investigation will be based on a randomized intervention, using three different aquatic-based exercise programs conducted in parallel for 28 weeks. The three programs include a continuous aerobic program, an interval aerobic program and a combined (aerobic and muscular strength) program. Variables related to cardiometabolic diseases will be evaluated, i.e., cardiovascular, mental health, and cognitive variables and biochemical markers.

All exercise programs will be conducted at the Piscina Muncipal da Sertã, two times a week (non-consecutive days), with 45-min sessions. All variables related to cardiometabolic diseases will be evaluated at two specific assessment moments: M1, before implementation of the physical exercise programs (baseline) and M2, after the conclusion of the 28 weeks aquatic-based physical exercise programs (post-intervention).

Each evaluation will be divided into three phases: Phase 1—Anthropometry evaluation, physical functions, cognitive and mental health levels; Phase 2—Evaluation of carotid arteries’ intima-media thickness and heart rate variability; and Phase 3—Evaluation of biochemical markers.

The blood collection for biochemical analysis will be conducted by a specialized and certified lab. The measurement of the carotid arteries intima-media thickness will be conducted by a specialist in the area of cardiology. All the remaining data will be collected and organized by the research team members.

### 2.2. Participants

The participants were recruited in the central area of Portugal, more specifically in the region of Sertã. The sample was recruited by the non-probabilistic method for convenience. One hundred and fifty individuals from the community were personally invited, but only 102 agreed to participate in the study (mean age of 72.32 ± 5.2 and BMI 29.47 ± 4.85). Participants will be selected according to the following inclusion criteria: individual of both genders; age equal to or above 65 years of age; non-institutionalized individuals; they give permission to be part of the study and if the participant presents with a clinical condition or comorbidity, it must be stable and enable participation in aquatic-based exercises classes as approved by local medical staff. The exclusion criteria are: individuals less than 65 years of age; individuals with medical diagnosed pathologies that jeopardize their health while preforming aquatic based exercises, participants that attend less than 50% of all the sessions and participants who cannot complete all of the proposed tests.

The participants will be distributed randomly into different exercise groups based on their registration for one of the schedules offered for the hydro-gymnastics sessions. There will be three distinct schedules (9.00, 9.50 and 10.40), with the constraint being that the participants must attend the same schedule for the whole year. The 9.00 session includes the continuous aerobic program, the 9.50 session includes the interval aerobic program, and the 10.40 session includes the combined exercise program. This information will not be provided to participants before they register for the sessions so it will not be possible to establish any association between the schedule and the different exercises programs. Such information will be communicated later in the study. The control group will be randomly recruited from the community and will include those individuals that have not been involved in any kind of physical exercise during the last year.

Before each assessment moment, participants will be taken to a testing room, where the assessment tests will be performed. The room will be large and isolated, and the temperature will be controlled, and each assessment stages should be organized to provide maximum comfort and privacy to the participants during the tests. The research team will give the participants information about the tests they will perform for data collection, explain the purpose of each test, and explain the order and duration of the tests. Participants will be able to question researchers about any doubts that they may have regarding the tests and any possible consequences. During the assessment, participants may pause the evaluation and continue on another day if they feel very fatigued or if they are not able to complete all the tests at that time. In this situation, a new date will be scheduled to continue the tests.

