### 2.3. Protocols

The percentage of adherence to the physical exercise programs, for each program, will be calculated considering the total attended sessions: (S × 100)/T, where “S” indicates the number of sessions that have been attended by the participant during the study and “T” indicates the total number (56) of physical exercise sessions. The participants’ attendance will be recorded in a database. If a participant has two consecutive absences, they will be contacted and given motivational reinforcement to incentivize them to resume their physical exercise sessions.

During the study period, all adverse effects or health problems attributed to the physical exercise sessions or evaluation tests will be reported. Parameters such as muscle pain, excessive fatigue and general pain will also be reported and inserted in a database. Exercise technicians and researchers will be responsible for data collection as well as for gathering and communicating all relevant data.

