*Maximum HR* is calculated with the following equation for senior populations [21]:(2)Maximum HR=207−(0.7×age)

The control group consists of non-institutionalized individual participants who have not partaken in any physical exercise during the preceding year. These participants will be encouraged to conduct their daily activities as usual, except for the data collection (M1 and M2) organized by the researchers.

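### The 50% attendance rule is written as an exclusion criterion, so it removes participants after allocation, and only from the three exercise groups

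*Protocol article*

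**What the plan says.** Section 2.2 (Participants) of the protocol article lists its exclusion criteria in one sentence. After age and health conditions that make aquatic exercise unsafe come "participants that attend less than 50% of all the sessions and participants who cannot complete all of the proposed tests".

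Section 2.3 (Protocols) defines attendance: "The percentage of adherence to the physical exercise programs, for each program, will be calculated considering the total attended sessions". The denominator T "indicates the total number (56) of physical exercise sessions". The same section describes the control group: "These participants will be encouraged to conduct their daily activities as usual", apart from the two data collections.

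Section 2.1 (Design) places all assessments at M1, before the programmes start, and at M2, after the 28 weeks. Section 2.2 does not say at which of these the test-completion clause applies. It also says that "participants may pause the evaluation and continue on another day" if they are fatigued or unable to finish.

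Section 2.6 (Statistical Analysis) compares groups by t-test or Mann–Whitney U test. It names no analysis set that would keep the participants whom section 2.2 excludes.

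**The concern.** An eligibility criterion should be decidable before the intervention begins. Attendance is behaviour during the intervention, and it exists in only three of the four groups. Using it to exclude people means that the exercise groups are filtered on something that may be related to health, motivation or response, while the control group passes through no such filter. The resulting difference between exercise and control mixes any effect of the programme with the effect of the filter.

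The three programmes can also be affected relative to one another. If one is attended less well, more of its participants are removed, and those who remain are a more selected group. Section 3 (Expected Results/Discussion) expects significant differences between the exercise groups, so this comparison matters too.

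A larger sample does not remove this kind of bias. If low attenders are not assessed at M2, their outcomes cannot be recovered later.

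**Working it through.** **1. The cut-off and when it can be known.** Sections 2.1 and 2.3 give 28 weeks and two sessions a week: 28 × 2 = 56, which agrees with the stated total. Half of 56 is 28, so a participant with 27 or fewer attended sessions is excluded. The earliest point at which this can be certain is after 29 absences (56 − 29 = 27). At two sessions a week, that falls in week 15 (29 / 2 = 14.5).

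**2. Who can be removed.**

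| Clause | Exercise groups | Control group | Timing |
|---|---|---|---|
| Attendance below 50% | Yes | No (no sessions) | During or after the programme |
| Cannot complete all tests | Yes | Yes | Not stated: M1 or M2 |

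Only the first clause is certain to act after allocation and on one side only.

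**3. Shift in the retained mean.** Let p be the fraction of an exercise group removed and g the gap in mean change, retained minus removed, in SD units. The full-group mean is (1 − p) × retained + p × removed, so

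retained mean − full-group mean = p × g.

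The document gives neither p nor g. The values below are assumptions.

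| p | g (SD) | Shift (SD) |
|---|---|---|
| 0.10 | 0.3 | 0.03 |
| 0.25 | 0.5 | 0.125 |
| 0.30 | 0.8 | 0.24 |

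If g = 0 the shift is zero whatever p is.

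**4. A second route to the size.** Assume no true effect, 25 participants per group, the lowest-attending fraction q removed from the exercise group only, and a correlation r between propensity to attend and change in outcome. The spurious difference is the mean of a truncated normal, r × φ(z_q) / (1 − q). The last column is the approximate chance of a false positive at a nominal two-sided 5%.

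| q | r = 0.1 | r = 0.3 | r = 0.5 | False-positive rate, r = 0.1 to 0.5 |
|---|---|---|---|---|
| 10% | 0.02 SD | 0.06 SD | 0.10 SD | 5.1% to 6.3% |
| 20% | 0.04 SD | 0.11 SD | 0.18 SD | 5.2% to 9.0% |
| 30% | 0.05 SD | 0.15 SD | 0.25 SD | 5.3% to 12.7% |

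The two routes give similar ranges: 0.03–0.24 SD and 0.02–0.25 SD. With r = 0 there is again no bias.

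**5. Between programmes.** The bias in a comparison of two programmes is p₁g₁ − p₂g₂. It cancels if removal and gap are alike. With an assumed common gap of 0.5 SD and removal of 10% in one programme and 30% in the other, it is 0.15 − 0.05 = 0.10 SD.

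**The case against.** Several points on the other side have force.

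- **An analysis plan not shown may define an intention-to-treat set.** This is possible. But the issue is a rule that the article states, not one it leaves out. A plan that kept these participants would contradict the exclusion criteria as written.
- **The test-completion clause may be an ordinary baseline screen.** This stands. The clause sits in an eligibility list, names no assessment moment and applies to all four groups. The option to finish on another day softens it. A reader might infer that both clauses are certain to act after allocation, or that one missed test discards a whole record. The text does not settle this. Those consequences follow only if the clause is applied at M2.
- **Poor tolerability would still be visible.** A reader might infer that the rule hides it. Section 2.3 has adherence calculated for each programme, has adverse effects, pain and fatigue recorded, and provides for contact after two consecutive absences. The outcome comparison can still be distorted, but the information is not lost.
- **The comparison with control is already weak.** This also stands. "The control group will be randomly recruited from the community" from people with no exercise in the past year, and the exercise groups form by registration for a time slot. Controls are therefore not an unselected group, and correcting the attendance rule does not make the contrast a randomised one. The rule adds a further bias to that separate problem.
- **Numbers.** A reader might take 76 / 4 = 19 per group, remove 25%, and conclude that about 14 remain in a trial already short of its loss allowance. Section 2.2 reports that 102 agreed to take part. If these include the controls and the groups are equal, that is about 25 per group, or about 19 after losing 25%. Whether 102 covers a 30% allowance on 76 depends on how it is applied (76 × 1.3 = 99; 76 / 0.7 = 109). That is a sample-size question on which this point does not rest.

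**Conclusion.** The point holds for the attendance clause. It is a stated exclusion rule that can be applied only after allocation and can remove participants only from the three exercise groups. The likely direction is in favour of exercise, but neither direction nor size can be derived from the document. Under the assumed removal of 10–30% and gap of 0.3–0.8 SD, the retained mean shifts by 0.03–0.24 SD. The shift is nil if attendance is unrelated to outcome.

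For the test-completion clause the conclusion is conditional. Used at M1 it is acceptable. Used at M2 it would select participants after allocation and would also discard outcomes that had been measured.

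**What to change.** - Remove the attendance clause from the exclusion criteria in section 2.2.
- Invite every enrolled participant to M2, whatever the attendance.
- Analyse each participant in the allocated group, outcome by outcome, with all available data.
- Keep the set with at least 50% attendance as a supportive analysis, labelled as such, and report attendance per programme over everyone enrolled in it.
- State that the test-completion clause is an M1 eligibility check, so that a test missed at M2 affects that outcome alone.

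The cost is a change of wording, M2 visits for low attenders who are already enrolled, and possibly a smaller estimated effect. The attendance data needed are already to be collected under section 2.3. The change does not cure the separate recruitment of controls or the formation of exercise groups by schedule registration, which need their own remedy.

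### The study is labelled randomised, but exercise groups form by self-registration for a class time and controls are recruited separately, so its group comparisons are open to confounding

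*Protocol article*

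**What the plan says.** The abstract describes chance allocation of one sample to all four arms: "The sample will be randomly divided into four groups, three experimental groups (EG) and one control group (CG". Section 2.1 repeats the label: "This investigation will be based on a randomized intervention".

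Section 2.2 then gives the mechanism for the exercise arms: "The participants will be distributed randomly into different exercise groups based on their registration for one of the schedules offered for the hydro-gymnastics sessions". The times are 9.00, 9.50 and 10.40, "with the constraint being that the participants must attend the same schedule for the whole year". Each time is tied to one programme: "The 9.00 session includes the continuous aerobic program, the 9.50 session includes the interval aerobic program", and the 10.40 class takes the combined programme. The stated safeguard is "This information will not be provided to participants before they register for the sessions".

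Controls come by another route: "The control group will be randomly recruited from the community", limited to people with no physical exercise in the past year. Section 2.3 repeats that restriction. The inclusion criteria in section 2.2 set no such condition for the exercise arms.

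Section 2.6 compares groups with independent-samples t-tests or Mann–Whitney U tests and mentions no adjustment for baseline values or covariates. Section 3 expects significant differences between exercise groups on some variables, and attributes the expected results to the aquatic environment and the exercise protocols.

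**The concern.** Randomisation means that chance, and neither the participant nor the investigator, decides the group. Here the participant's own booking decides which exercise programme is received, and the recruitment route decides who is a control. The article states its method of allocation, so this is not a detail left to a fuller document; the stated method contradicts the stated label.

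Two comparisons are at stake. Between programmes, people who prefer different class times may differ in ways that affect the outcomes, and slot and programme coincide completely. Between exercisers and controls, one side signed up for classes and the other was selected for a year without exercise. Readers and evidence syntheses would take the label at face value and read a difference as a causal effect of the programme.

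**Working it through.** No figure in the plan bears on allocation, so there is none to reproduce. The main check sets the statements side by side.

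1. **Label.** The abstract claims chance division of one sample into four groups; section 2.1 claims a randomised intervention.
2. **Exercise arms.** Section 2.2 names registration for a class time as the basis of allocation. It describes no sequence, list or draw, either for people to slots or for programmes to slots. Adding the word randomly to that sentence does not supply one.
3. **Control arm.** Section 2.2 recruits controls separately, under an inactivity condition not listed for exercisers. Even a random draw from the community would be random sampling of a different population, not random allocation from a common pool. The abstract's four-group statement therefore fails whatever is decided about the slots.
4. **Safeguard.** Withholding programme content removes choice by programme preference. It does not remove differences between people who prefer different times, and it does not touch the control group.
5. **Analysis.** The between-group tests in section 2.6 state no adjustment that would reduce such differences.

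**Illustration of consequence (assumed inputs).** Suppose the true programme effect is zero, but people in two slots differ by d SD in the outcome being analysed. For a two-sided 0.05 t-test with n per group, the noncentrality is d × √(n/2) on 2n − 2 degrees of freedom, and the rejection rate follows from the noncentral t distribution.

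- Section 2.2 reports 102 people who agreed to take part. An equal four-way split gives 102/4 = 25.5, taken as 25; the document does not give the split. If all 102 were in the three exercise arms, n = 102/3 = 34.
- The values of d are assumptions. The documents give no data by slot.

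| d (SD) | noncentrality, n = 25 | false-positive rate, n = 25 | noncentrality, n = 34 | false-positive rate, n = 34 |
|---|---|---|---|---|
| 0 | 0 | 5% | 0 | 5% |
| 0.2 | 0.71 | 11% | 0.82 | 13% |
| 0.3 | 1.06 | 18% | 1.24 | 23% |
| 0.5 | 1.77 | 41% | 2.06 | 53% |

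The table shows how sensitive one unadjusted pairwise test would be. It does not estimate the bias in this study.

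**The case against.** The best defence is that slot choice may be close to arbitrary. Participants do not know the programme when they register, and the first and last classes start only 100 minutes apart. No baseline data by slot are given, and particular reasons for preferring one time over another are conjecture. Section 2.6 also does not say whether groups are compared on M2 values or on change from M1. If on change, a stable baseline gap would cancel and only a difference in trajectory would matter. Finally, covariate adjustment could be set out in an analysis plan that is not shown.

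Much of this stands as a limit on size. A reader might infer that the programme comparisons are in fact confounded, or that a particular amount of bias can be attached to them. The documents support neither; they show exposure to confounding, of unknown size and direction. A reader might also infer that the main aim is to rank the programmes and is therefore lost. The stated aim is to assess the programmes' impact on risk markers, with differences between exercise groups a further expectation in section 3.

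None of this supplies a chance mechanism, and the defence does not reach the control group at all. An unseen analysis plan could add adjustment, but it could not make registration and separate recruitment into randomisation.

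**Conclusion.** The point holds as a contradiction between label and mechanism. As described in section 2.2, none of the four groups is formed by random allocation, so the abstract and section 2.1 are wrong as written. Both the between-programme and the exercise-versus-control comparisons are open to confounding, and the stated tests offer no protection. This conclusion rests on the text alone and needs no numerical assumption.

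The rise from 5% to about 11% to 41% for one pairwise test depends on an assumed difference of 0.2 to 0.5 SD in the analysed outcome, 25 per group and no true programme effect.

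**What to change.** - In the abstract and sections 2.1 and 2.2, replace the randomisation wording with a description of a non-randomised parallel-group study, covering all four groups.
- In section 2.6, replace the unadjusted between-group tests with a comparison adjusted for the M1 value and baseline variables already available. Age and BMI (reported in section 2.2) and sex (needed for the arm-curl weights in section 2.4.4) are examples.
- In section 3, word conclusions as associations. State that slot and programme cannot be separated, and that adjustment reduces self-selection bias without removing it.

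Section 2.2 reports recruitment as done but allocation as still to come. If allocation is still open, a computer-generated list could assign people to the exercise groups. That alone would not justify the four-group label: controls would have to be allocated from the same pool by the same list. It would also leave each programme tied to one class time.

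Relabelling and adjustment cost a weaker design label and slightly more analysis. Using a list would cost an allocation procedure and possibly some participants who cannot attend the assigned time; including the controls would also mean changing how they are recruited.
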